### Surgical intervention

All participants will receive a Triathlon TKR with a highly crossed linked (X3) cruciate retaining polyethylene insert. This is the current standard care for both participating surgeons. All participants will receive standard post op nursing and rehabilitation care. Prior to discharge from hospital patients will undergo the routine physiotherapy and occupational assessments for activities of daily living and equipment will be provided as routine.

Patients randomised to standard will receive a conventional manual Triathlon TKR with a highly crossed linked (X3) cruciate retaining polyethylene insert. In a manually performed TKR, the surgeon will make an incision down the front of the knee and move the knee cap to one side to allow access to the knee joint. The surgeon will then make bone cuts using a manual jig-based system and a hand held saw to prepare the bone surfaces for the implant. A measured resection technique will be employed with 8-mm resection from the distal femur and 9mm from the proximal tibia with a 3° slope. Both surgeons will use a conventional jig alignment technique for intramedullary referencing for the femur and extra medullary referencing for the tibia. Sizing of the femoral component and rotation (using Whiteside’s line [29]) will be performed manually after intra-operative assessment. Once the implant is in position the knee is then balanced by the ‘feel’ though a range of movement and soft tissue releases will be performed as required to balance the knee in flexion and extension.

The intervention group (undergoing robotic-arm-assisted surgery) will require a pre-operative CT scan as part of the planning process for robotic-assisted surgery. The information from the CT scan will be used to create a 3D model of the patient’s bony anatomy to plan the positioning and sizing of the implant. The research team will make every effort to coordinate the CT scan with the patient’s routine pre-assessment clinic to limit the requirement for additional hospital visits. The CT scan will be anonymised using a dedicated study code and transferred to Stryker using an encrypted data drop box. The CT scan will be reconfigured and transferred back using an encrypted data drop box. This data will be used by the MAKO technician to plan the individuals’ surgery. The participants will receive the same Triathlon TKR with a highly crossed linked (X3) cruciate retaining polyethylene insert and the same surgical approach to the knee joint will be employed. Instead of using a manual jig-based system and a handheld saw to prepare the bone surfaces for the implant, the MAKO robotic-arm will be used by the surgeon to cut the bone at the required alignment. The MAKO is a robotic arm that the surgeon guides to cut the diseased bone instead of using a manual jig and the handheld saw. The information from the CT scan will be used to create a 3D model of the patient’s bony anatomy and will used to plan the positioning of the implant. During the operation, trackers (markers for the robot to assess where the knee is in space) will be positioned on the tibia and femur using two treaded pins (4mm) through a small incision (2cm) a hands width above and below the joint. Once the trackers are in place, registration of the knee joint surface is performed. The specified bone cuts are then performed using the robotic arm. The specified bone cuts will be 5° of valgus and neutral flexion/extension for the femoral component and zero varus/valgus with 3° of posterior slope for the tibial component relative to the mechanical axis. When the implant is in place, the Verasense^TM^ (OrthoSensor Inc. Dania Beach, FL, USA) will then be inserted into the knee joint. Pressures in the medial and lateral compartments will be recorded throughout a range of movement (extension to flexion). Soft tissue releases will be performed as required to balance the knee, defined as a pressure difference of less than 15Ibs in medial and lateral compartments, throughout a range of motion [16].

All patients will receive the same standard of inpatient care and rehabilitation and discharge advice to progress mobility and standard exercises. Data will be collected from source data regarding LOS and discharge details. Data regarding health care usage and equipment will be collected using the modified CSRI completed at follow-up clinics and interim phone call follow-ups. The research team will contact the patient by phone and at scheduled research visits to optimise completion over the study period.

### CT scan

CT is a procedure that uses x-ray equipment to create cross-sectional pictures of bony anatomy. During the scan, the participant will lie on a narrow platform bed as it slides through the scanner, which is shaped like a large donut. A CT scanner creates clear and detailed pictures of bones. CT scans involve radiation and there are small risks associated with radiation exposure. These are described in patient information leaflet. The CT scan is an essential component of the research study and provides the anatomical information required for the MAKO robot to accurately perform the bone cuts during surgery. If a patient is unable to undergo a CT scan for any reason, then they are unable to participate in the research study.

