### Eligibility criteria

Participants listed for routine primary TKR for osteoarthritis under the care of the two participating surgeons at the institution will be screened for inclusion. The inclusion criteria are as follows: planned to undergo a primary TKR for end-stage osteoarthritis under the care of the two participating surgeons, age 45–85 at the time of listing for surgery, and suitable candidate for a cruciate retaining TKR (Triathlon prosthesis). The exclusion criteria are as follows: varus deformity of > 20° observed by consultant on examination, patient is unable to comply with the study protocol (incl. refusal for CT scan), female participants who is pregnant, lactating or planning pregnancy during the course of the study, requires patella resurfacing, inability to understand the patient information for the study, provide written informed consent or answer study questionnaires for cognitive or language reasons, or any other significant disease or disorder which, in the opinion of the Investigator, may either put the participants at risk because of participation in the study or influence the result of the study, or the participant’s ability to participate in the study.

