### Recruitment

Patients listed for a routine primary TKR under the care of the participating surgeons will be screened by the treating clinician. A screening form will be completed to confirm name, age, hospital number, listed for routine primary TKR, suitable candidate for a cruciate retaining TKR (Triathlon prosthesis), no varus deformity of > 20°, capacity to provide informed consent and no pre-existing condition that limits function and potential outcome of surgery. After making the initial approach, the consultant will request the patient’s permission to be approached by the research team who will provide the patient information sheet, discuss the study in more detail and confirm eligibility. Patients will be encouraged to take the study information and discuss with their family and friends before making a decision to participate. The research team will reconfirm the eligibility criteria below and record that: the patient is able to comply with the study protocol (incl. refusal for CT scan) and that female participants are not pregnant, lactating or planning pregnancy during the course of the study.

Eligible patients are identified by the treating consultant surgeon and listed for surgery and a screening form is completed but are not approached at that time will be sent a letter of approach from the consultant along with the patient information sheet. The research team will then contact the patient to discuss the study in more detail and answer any questions. All eligible patients who agree to participate in the study will be invited to attend a research clinic to provide written informed consent and complete baseline assessments before randomisation.

Participants will be asked to attend a research appointment to provide written informed consent and complete a CRF and a number of pre-operative questionnaires recording their knee function, expectations and general health. Participants will be asked to carry out a gait assessment which involves walking over an instrumented walkway (Tekscan instrumented mat system, Tekscan Inc. Boston, USA) that is 3 m long plus 1 m either side, six times and standing still on an individual instrumented mat of the walkway for 1 min. After completing the baseline assessments participants will be randomised to one of two groups. Patients will be informed of their allocation and the research staff will reinforce the treatment allocation and arrange a CT for those randomised to the intervention group.

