All participants will attend a routine pre-assessment clinic 4–6 weeks prior to surgery to assess fitness for surgery. Pre-assessment staff will be notified of the patient’s inclusion in the study and their group allocation. Participants randomised to the robotic-assisted surgery group will be required to have an additional CT scan which may be arranged to coincide with this appointment. At this routine clinical appointment, the research team will ensure all baseline data is complete and ensure the patient has no concerns. The CT scan will be anonymised using a dedicated study code and transferred to Stryker using an encrypted data drop box. The CT scan will be reconfigured and transferred back using an encrypted data drop box. This data will be used by the MAKO technician to plan the individuals’ surgery. This process is standard practice in hospitals across the UK already using the MAKO for robotic-assisted knee surgery.

All participants will be admitted in line with routine practice. Surgical data and hospital discharge data will be collected from source data to complete the CRF during the inpatient stay. No additional research assessments will be carried out at this point.

All participants will attend a routine 3-month post-surgery assessment with the clinical team including knee radiographs. Participants will also be seen by the research team to complete the relevant patient-reported questionnaires, Health service resource use and complications data forms.

All participants will be asked to attend an additional 6-month post-surgery research visit to complete the relevant patient-reported questionnaires, health service resource use and complications data forms. The gait assessment carried out at baseline will be repeated.

A member of the research team will contact the participant by telephone at 9 months following surgery to complete the health service resource use questionnaire as this only captures data over the previous 3 months.

All participants will attend a routine 12-month post-surgery assessment with the clinical team including knee radiographs. Participants will also be seen by the research team to complete the relevant patient-reported questionnaires, health service resource use and complications data forms. A gait analysis assessment will also be carried out.

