### Defined end of trial

The end of trial is the date of the 12-month follow-up visit of the last participant. Each participant has the right to withdraw from the study at any time. In addition, the investigator may discontinue a participant from the study at any time if the investigator considers it necessary for any reason including ineligibility (either arising during the study or retrospective having been overlooked at screening); significant protocol deviation, i.e. intervention not used as intended at time of surgery; significant non-compliance with treatment regimen or study requirements; an adverse event which requires discontinuation of the study medication or results in inability to continue to comply with study procedures; consent withdrawn; or lost to follow-up.

Participants who wish to withdraw consent for the trial or whose participation from the trial is discontinued will have anonymised data collected up to the point of that withdrawal of consent included in the analyses unless the participant specifically asks for all data collected to be destroyed. No additional data will be collected from the participant. The reason for withdrawal will be recorded in the CRF. Participants who withdraw once they have been randomised will not be replaced. If the participant is withdrawn due to an adverse event, the investigator will arrange for follow-up visits or telephone calls until the adverse event has resolved or stabilised.

At the end of the trial, patient will resume standard practice of care of the study centre in place at that time for follow-up of routine TKR.

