## Discussion

This study aims to assess whether the improved accuracy of implant alignment using robotic arm-assisted surgery and the Verasense^TM^ (OrthoSensor Inc. Dania Beach, FL, USA) aids the surgeon to balance the TKR intraoperatively results in a greater improvement in the early knee-specific outcome. In addition, the secondary outcomes assessed in this study will enable quantification of the patient’s expectations fulfilment, improvement in their general health, restoration normal gait and patient satisfaction. Furthermore, the study aims to assess whether robotic arm-assisted TKR is a cost-economically viable treatment within the National Health Service in the UK.

The major limitation of the study design is the non-blinding of the patients to the intervention that they will receive, and this may bias the patient-reported outcomes measures assessed. The reason for this is due to the need for a pre-operative CT scan in those patients randomised to undergo robotic arm-assisted TKR and associated radiation exposure; therefore, patients needed to be informed of this prior to enrolling to the study. The authors considered performing placebo CT scans for those undergoing manual TKR using jig-based systems to enable blinding of the patients, but this was not possible due to the fact patients would be exposed to a significant dose of radiation that would be of no benefit to the patient. The assessors were blinded to the intervention arm, but the majority of the outcome measures assessed in this study are subjective patient reported outcomes.

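### The CT condition for taking part has no time limit, yet the CT is attempted only after randomisation and only in the intervention group, so eligibility-based discontinuation can cost 6-month outcomes in that group alone

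*Protocol article*

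**What the plan says.** Four parts of the protocol article bear on this.

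- **Condition of participation.** The CT scan section states: "If a patient is unable to undergo a CT scan for any reason, then they are unable to participate in the research study". It names neither a time point nor a group.
- **Screening.** Eligibility criteria lists as an exclusion: "patient is unable to comply with the study protocol (incl. refusal for CT scan". Recruitment has the research team reconfirm eligibility and record that "the patient is able to comply with the study protocol (incl. refusal for CT scan". Both steps apply to every candidate and come before allocation.
- **Sequence.** Recruitment says: "After completing the baseline assessments participants will be randomised to one of two groups". Patients then learn their allocation, and staff "arrange a CT for those randomised to the intervention group". The same section adds: "Participants randomised to the robotic-assisted surgery group will be required to have an additional CT scan which may be arranged to coincide with this appointment". That appointment is the pre-assessment clinic, 4 to 6 weeks before surgery. The control group is never scanned: the Discussion reports that a placebo scan was weighed and ruled out because of the radiation dose.
- **After randomisation.** Defined end of trial allows the investigator to discontinue a participant on several grounds, one of them "ineligibility (either arising during the study or retrospective having been overlooked at screening". Data up to that point are kept unless the participant asks for their destruction. Nothing further is collected, and participants who withdraw after randomisation are not replaced.

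**The concern.** An eligibility condition does no harm to a randomised comparison if it is settled for everyone before allocation. It does harm if it can be applied afterwards in one group only. Here the scan itself is the only direct test of whether a patient can and will have it, and that test takes place with allocation known and in the intervention group alone.

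Take two patients who both agree to the CT at screening and who would both later prove unable to have it or change their minds. In the intervention group the problem surfaces, and the patient then fails a stated condition of participation. The discontinuation clause gives the investigator a ground to end that patient's participation, and the 6-month WOMAC function score is lost. In the manual group the same problem is never detected, and the patient is followed to 12 months.

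At stake is the comparability of the two groups on the primary outcome. An analysis plan cannot repair this by defining an intention-to-treat set, because the outcome would not have been collected.

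**Working it through.** **1. Sequence for each group**

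| Step | Intervention | Manual |
|---|---|---|
| CT refusal screened before randomisation | yes | yes |
| CT booked after allocation | yes | no |
| Later inability or change of mind can be seen | yes | no |
| Discontinuation for ineligibility arising during the study can apply on this ground | yes | no |
| 6-month WOMAC lost if it is applied | yes | does not arise |

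The groups are treated alike up to randomisation and differ from the second row on.

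**2. The plan's own sample size**

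Inputs from Sample size: difference 15, SD 26.5, one-sided alpha 0.05, power 80%, loss 10%.

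- Normal approximation: n per group = 2 × (1.645 + 0.842)² × (26.5/15)² = 38.6, so 39.
- One-sided t-test: 39.3, so 40 per group and 80 in all, as stated.
- Allowance for loss: 40/0.9 = 44.4, so 45 per group and 90 in all, as stated.

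The figures reproduce. I therefore take 45 per group as the expected split under 1:1 allocation.

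**3. Size of a one-sided removal (illustration)**

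The document gives no rate of CT failure after randomisation and no prognosis for such patients. Both are assumptions here. Let k be the number removed from 45, and let each be 15 points worse than the group mean.

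Shift in the mean of those remaining = k × 15 / (45 − k)

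- k = 1 (2.2% of 45): 15/44 = 0.34 points
- k = 3 (6.7% of 45): 45/42 = 1.07 points

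If the gap D is instead measured between removed and retained patients, the shift is (k/45) × D. For D = 15 this gives 0.33 (k = 1) and 1.0 (k = 3). Over a wider grid, from k = 1 with D = 10 to k = 5 with D = 26.5, it runs from 0.22 to 2.94 points.

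For scale, the standard error of the difference with 40 per group is 26.5 × √(2/40) = 5.9 points. A shift of 1.07 is 0.18 of that, and 7% of the 15-point target.

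**4. Effect on power**

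Power = Φ(15 / (26.5 × √(1/n₁ + 1/n₂)) − 1.645), with 10% general loss in both groups.

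- k = 0: n = 40.5 and 40.5, power 81.7%
- k = 3: n = 40.5 and 37.8, power 80.5%

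Loss of power is negligible. What matters is that the removal would be selective.

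**The case against.** The strongest case on the other side is that the CT scan section is written as an entry condition. It matches the exclusion criterion and contains no instruction to withdraw anyone. Both groups are screened for CT refusal before allocation, and the Discussion says patients had to be told about the scan before enrolling. Removal needs a separate, discretionary clause. All of this stands, and it confines the problem to inability or a change of mind that emerges between randomisation and the scan. It does not close that gap, because the condition carries no time limit and the discontinuation clause expressly reaches ineligibility that arises during the study.

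A reader might infer more than the text supports:

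- *That the CT scan section itself expels randomised patients.* It does not. Only the discontinuation clause can, and only if the investigator chooses to use it.
- *That the exclusion criterion covers refusal alone.* Refusal is introduced as one example of inability to comply, so a patient who cannot have the scan is covered as well.
- *That the pre-randomisation check is reversed and so fails.* The wording in Recruitment does list refusal under ability to comply, but it reads as a parenthesis carried over from the exclusion criterion. It is an editorial slip, not evidence that refusers are admitted.
- *That a missed scan ends participation.* A missed appointment is not inability, and nothing in the text says so.
- *That the bias favours the robotic procedure.* That is plausible if patients who cannot complete the scan would do worse, but the document has no information on their outcomes.

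It may also be said that the analysis set belongs in the full protocol or the analysis plan. That is fair, and its absence is not the point here. The point is a follow-up rule that the article does state.

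**Conclusion.** The concern holds in a limited form. Read together, the undated CT condition and the discretionary discontinuation clause permit a post-randomisation exclusion that can occur in the intervention group only and that costs the 6-month WOMAC. The text does not require that exclusion, and screening in both groups makes it uncommon.

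The number affected is not given and is probably small. With an assumed 1 to 3 of 45 removed, each 15 points worse than the group mean, the shift is about 0.3 to 1.1 points against a 15-point target, with direction uncertain. That would be unlikely to change the trial's conclusion by itself. The change is still worth making, because it removes a one-sided exclusion at almost no cost and an outcome never collected cannot be recovered in analysis.

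**What to change.** Reconcile four sections so that they state one rule:

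- **Eligibility criteria and Recruitment:** willingness and ability to have a CT is confirmed and recorded for every patient before randomisation.
- **Recruitment:** reword the recorded item so that it no longer lists refusal under ability to comply.
- **CT scan:** say that the condition applies at that pre-randomisation point only.
- **Defined end of trial:** say that not having the CT after randomisation is not a ground for ending follow-up. Such patients are followed to 12 months and analysed in their allocated group unless they withdraw consent.

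The cost is wording in the protocol and the screening form. The downside is slight dilution of the difference, because a few patients in the intervention group may not have had the intervention as planned.

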### Safety reporting

The risks for the two groups are those particular to TKR and from an operative intervention. This includes infection, thrombosis, stiffness, instability, pain, scar sensitivity, loss of function, nerve or vessel injury, requirement for revision with attendant time off work. General risks include cardiorespiratory risk, angina, MI, stroke, pneumonia, risks from prolonged recumbency, urinary infection, skin ulcers. Potential risks and steps taken to minimise these risks are outline in the PIL. In addition it is anticipated that those patients with patients who are randomised to use of the robotic instrumentation may require a longer procedure of up to 5 min [10], and there is a theoretical increased risk of infection. There is also a small (1%) risk of sustaining a fracture through a tracker pin (a threaded pin inserted into the bone so the robot can establish the position of the bone in time and place) [30, 31]. Tracker pins are routinely used for navigated TKR surgery and this increased risk is accepted to enable more accurate placement on the knee prosthesis. However, to our knowledge, there is no reported case of a fracture through a tracker pin site when used for robotic TKR surgery. There is also a small risk (1%) of wound infection at the site of tracker pins, but again these are established and accepted in navigation TKR surgery [32].

An adverse event (AE) is any untoward medical occurrence in a patient or other clinical investigation participant taking part in a trial of a medical device, which does not necessarily have to have a causal relationship with the device under investigation. An AE can therefore be any unfavourable and unintended sign (including an abnormal laboratory finding), symptom or disease temporally associated with the use of the device, whether or not considered related to the device.

An adverse device effect (ADE) is all untoward and unintended responses to the medical device. The phrase ‘responses to a medical device’ means that a causal relationship between the device under investigation and an AE is at least a reasonable possibility, i.e. the relationship cannot be ruled out. All cases judged by either the reporting medically qualified professional or the sponsor as having a reasonable suspected causal relationship to the device qualifies as a device effect. This also includes any event resulting from insufficiencies or inadequacies in the instruction for use or deployment of the device and includes any event that is a result of a user error.

A device deficiency (DD) is inadequacy of a medical device related to its identity, quality, durability, reliability, safety, or performance, such as malfunction, misuse or use error and inadequate labelling.

‘Serious’ in serious adverse event (SAE) means an adverse event resulting the following: death, in-patient hospitalisation or prolonged hospitalisation (defined as an inpatient admission, regardless of length of stay). However, hospitalisation for pre-existing conditions (including elective procedures that have not worsened) or additional elective hospitalisation does not constitute a SAE. A life-threatening illness or injury in the definition of ‘serious’ refers to an event in which the participant was at risk of death at the time of the event; it does not refer to an event which hypothetically might have caused death if it were more severe. Persistent or significant disability or incapacity. Congenital anomaly or birth defect. Other serious events that may jeopardise the patient and may require medical or surgical intervention to prevent one of the other five listed outcomes. This includes device deficiencies that might have led to an SAE if suitable action had not been taken, intervention had not been made or if circumstances had been less fortunate.

To ensure no confusion or misunderstanding of the difference between the terms ‘serious’ and ‘severe’, which are not synonymous, the following note of clarification is provided: The term ‘severe’ is often used to describe the intensity (severity) of a specific event (as in mild, moderate, or severe myocardial infarction); the event itself, however, may be of relatively minor medical significance (such as severe headache). This is not the same as ‘serious’, which is based on patient/event outcome or action criteria usually associated with events that pose a threat to a participant’s life or functioning. Seriousness (not severity) serves as a guide for defining regulatory reporting obligations.

A serious adverse device effect (SADE) is any untoward medical occurrence seen in a patient that can be directly related to the Stryker product resulting in resulting in any of the characteristics or led to characteristics of a serious adverse event. SADE is also any event that may have led to these consequences if suitable action had not been taken or intervention had not been made or if a circumstance has been less opportune. All cases judged by either the reporting medically qualified professional or the sponsor.

Anticipated serious adverse device effect (ASADE) which by its nature, incidence, severity or outcome has been previously identified in the current version of the risk analysis report or Investigator Brochure.

Unanticipated adverse device effect (UADE) is any serious adverse device effect on health or safety or any life-threatening problem or death caused by or associated with a device, if that effect, problem or death was not previously identified in nature, severity or degree of incidence in the investigational plan or application (including a supplementary plan or application), or any other unanticipated serious problem associated with a device that related to the rights, safety or welfare of the subject.

Tables 1 and 2 categorise the adverse event according to whether it is related to the device. Each AE will be assessed for seriousness, severity, causality and expectedness by an appropriately trained and delegated investigator. The Investigator, or an appropriately trained designee, should make an assessment of seriousness using the criteria in Table 3.

**Table 1 Tab1:** Classification of adverse event according to relation to the device (robot)

Adverse Events	Non-device related	Device or procedure related	
**Non-serious**	AE	ADE	
**Serious**	SAE	SADE	
		Anticipated	Unanticipated
		ASADE	USADE

**Table 2 Tab2:** Device deficiency category according to SADE

Device deficiency	Could lead to a SADE	Would not lead to a SADE
**Category:**	Device deficiency with SADE potential	Device deficiency without SADE potential

**Table 3 Tab3:** Classification criteria for the intensity of the adverse event

Intensity	Description
Mild	An event easily tolerated by the patient, causing minimal discomfort and not interfering with everyday activities
Moderate	An event sufficiently discomforting to interfere with normal everyday activities
Severe	An event that prevents normal everyday activities

The expectedness of the AE will be assessed by the CI or an appropriately trained designee using the list of expected events below. This list is based on current clinical knowledge of expected intra- and post-operative complications of TKR. Intra-operative complications: not able to proceed with expected implant (in this case triathlon TKR), soft tissue damage, neurovascular damage, fracture, patients becomes medically unwell and cannot perform TKR, blood loss and general medical complications, e.g. heart attack, stroke. Post-operative complications: infection (superficial and deep implant infection), deep vein thrombosis and pulmonary embolus, stiffness, swelling, numbness, neurovascular complications, wound breakdown, fracture and general health problems, e.g. stroke, heart attack, kidney failure and potential loss of limb and life.

The relationship between the investigational medical device (including comparator treatments) and the occurrence of each AE must be assessed and categorised by the Chief Investigator (or delegate). Related events are those that are related to the administration of the medical device or study procedures. Each AE will be categorised as (1) not related (no relationship with the investigational device; other factor(s) certainly or probably causative) or (2) possibly related (the nature of the event, underlying medical condition, concomitant medication or temporal relationship make it possible that the AE has a causal relationship to the device).

All AE’s occurring during the study observed by the investigator or reported by the participant, whether or not attributed to the device under investigation will be recorded on the CRF as specified in the protocol. All ADE’s will be recorded in the CRF. The following information will be recorded: description, date of onset and end date, severity, assessment of relatedness to device, other suspect drug or device and action taken. Follow-up information should be provided as necessary. The relationship of AEs to the device will be assessed by a medically qualified investigator or the sponsor/manufacturer and will be followed up until resolution or the event is considered stable.

All ADE that result in a participant’s withdrawal from the study or are present at the end of the study should be followed up until a satisfactory resolution occurs. All DDs should be reported to NUTH via the safety reporting inbox: [contact]

All SAEs/SADEs/ASADEs/UADEs will be reported to the CI in the first instance, who will determine seriousness, relatedness and expectedness. The event will then be reported to the sponsor/legal representative NUTH R&D Regulatory Compliance Team at [contact] within one working day of the investigator team becoming aware of them. For a related serious adverse event (SAE) the investigator will complete a Stryker ‘Product Experience Report’ form *(**www.stryker.com**product experience report)* or inform a Stryker employee*.*

Reports of related and unexpected SAEs will be submitted to ethics within 15 days of the Chief Investigator becoming aware of the event, using the NHS HRA Non-CTIMP Safety Report to REC form (Report of Serious Adverse (non-CTIMP) Form). Related and unexpected events must also be reported through the NUTH DATIX Incident Reporting System by a member of the research team. USADEs occurring in NUTH sponsored studies must also be reported via the electronic incident reporting system, DATIX. The incident type should be entered as ‘Research Incident/Accident’, Directorate as ‘Medical Director’s Directorate’, Speciality as ‘Research Development and Governance’, Site as ‘Regent Point’ and Location as ‘Research Buildings’. The event must also be assessed by the CI to determine whether or not it constitutes a serious incident (SI). This is defined as an event or incident that resulted in unexpected or avoidable death, or serious harm, to one or more patients, staff, visitors or members of the public. If the event has been classed as (or is suspected to be) a SI, an NUTH NHS Foundation Trust manager will inform the Director of Quality and Effectiveness, via. the Clinical Governance and Risk Department (CGARD), as soon as possible by telephone. This is detailed in the NUTH FT ‘Serious Incident Reporting and Management Policy’.

If an ADE is defined as serious (i.e. a SADE) or a DD that could have led to a SADE/USADE, the investigator will quarantine the device as soon as possible. This involves segregating the device from other equipment and labelling it as ‘not for use’ with relevant contact details of the research team. The device and all associated items (including relevant packaging materials) should be quarantined. They should not be repaired, discarded, or returned to the manufacturer without agreement from Sponsor.

